## **3) Follow up**

A follow up session will be conducted at second meeting (four weeks after first meeting). In the intervention group, the respondents will be gathered in a group for a sharing and question and answer (Q & A) session. For respondents who manage to perform foot self-care behaviour effectively will be asked to be a mentor and share their skills and experiences with others. The objective of this session is to sustain the self-efficacy level of elderly with diabetes to continue performs foot self-care behaviour regularly. A specific guidance and motivation will be given individually if there is any respondent who do not able to perform foot self-care behaviour effectively. Whereas, the control group will only receive a regular visit from the researcher. Both intervention and control group will be assessed (second measurement) with the questionnaire (DFSBS, FCCS, FCOE, KFC, FS-QOL).

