| Week 4                              | Visit, question and answer session, continuously give guidance and motivation on foot self-care behaviour. The respondents need to fill in the questionnaire; DFSBS, FCCS, FCOE, KFC, FS-QOL                                                                                                                                                                                                                                                                                                                                        | Regular visits. The respondents need to fill in the questionnaire; DFSBS, FCCS, FCOE, KFC, FS-QOL                                                                           | Discussion
Questionnaire | 20 minutes |
| Week 5, 6, 7, 8, 9, 10, 11          | Follow up to the health provider                                                                                                                                                                                                                                                                                                                                                                                                                                                                                                    | None                                                                                                                                                                        | Phone call                  | 5 minutes  |
| Week 12                             | Evaluation
Last visit. Keep reminding to maintain the foot self-care behaviour among the elderly
The respondents need to fill in the questionnaire; DFSBS, FCCS, FCOE, KFC, FS-QOL                                                                                                                                                                                                                                                                                                                                            | Evaluation
Last visit. Keep reminding to maintain the health care among the elderly
The respondents need to fill in the questionnaire; DFSBS, FCCS, FCOE, KFC, FS-QOL | Discussion
Questionnaire | 20 minutes |

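### At week 4 the intervention arm's coaching is listed before the T2 questionnaire at the same visit, and nothing requires the questionnaire to come first

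*Combined protocol and SAP*

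**What the plan says.** **Week 4, intervention arm.** The Table 3.4 row (section 3.7.2) reads: "Visit, question and answer session, continuously give guidance and motivation on foot self-care behaviour. The respondents need to fill in the questionnaire". Section 3.7.2, 3) Follow up, gives the detail. First, "the respondents will be gathered in a group for a sharing and question and answer (Q & A) session", with residents who are doing well acting as mentors. Then: "A specific guidance and motivation will be given individually if there is any respondent who do not able to perform foot self-care behaviour effectively". The section's last sentence is the measurement: "Both intervention and control group will be assessed (second measurement) with the questionnaire".

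**Week 4, control arm.** Table 3.4 has: "Regular visits. The respondents need to fill in the questionnaire". No coaching is listed.

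**Week 12.** Table 3.4 heads both cells with the word Evaluation. The intervention cell continues: "Last visit. Keep reminding to maintain the foot self-care behaviour among the elderly". The control cell continues: "Last visit. Keep reminding to maintain the health care among the elderly". The questionnaire is named last in both. Section 3.7.2, 4) Evaluation (post-test), mentions no group session or coaching at that visit.

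**Timing.** Section 1.5.2 defines T2 and T3 as 4 and 12 weeks after the education program. No section says whether the questionnaire precedes or follows the session or reminder.

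**The concern.** T2 is meant to show what remains four weeks after the seminar. If a resident has just sat through peer accounts, questions and individual advice on foot care, the answers also reflect that hour. Only the intervention homes have this session, so its same-day effect coincides exactly with arm. The mixed ANOVA in Table 3.5 cannot separate the two.

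The bias would favour the programme, and the outcomes differ in exposure:

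- **Knowledge (KFC), efficacy expectation (FCCS), outcome expectation (FCOE).** These ask about present knowledge and confidence. Section 3.6.1 requires the KFC and FCOE content to match the education package, so what is tested is what may just have been discussed.
- **DFSBS, the primary outcome.** It is self-reported. Items 1 to 7 count days over the past week. Items 8 to 16 ask what the resident generally does, with no window.
- **Setting.** The researcher knows the allocation (section 3.3) and interviews residents who cannot read or write (section 3.6.1). Both add to the pull towards a desirable answer.

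**Working it through.** **1. Order of activities, side by side**

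| Visit | Intervention | Control | Same-day difference between arms |
|---|---|---|---|
| Baseline | Questionnaire, seminar later | Questionnaire | None |
| Week 4 | Group session, guidance, then questionnaire (as listed) | Visit, questionnaire | Coaching in one arm only |
| Week 12 | Foot self-care reminder and questionnaire | General health reminder and questionnaire | Content of the reminder |

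Baseline is taken before any teaching. The listed order at week 4 would therefore measure T2 under different conditions from T1, in one arm.

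**2. Exposure by instrument**

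- DFSBS: 9 of 16 items (8 to 16) have no recall window.
- KFC: section 3.6.1 scores 11 questions, so one item is worth 1/11 = 9% of the scale. The appendix prints 12 rows, which would make it 1/12 = 8%.
- The quality-of-life scale looks back four weeks.

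**3. The plan's own figure.** Inputs from section 3.5.2: difference 36.22 − 32.32 = 3.90, SD 6.76, two-sided 5%, power 80%, design effect 1.25.

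n = 2 × 6.76² × (1.96 + 0.842)² / 3.90² = 47.18; the plan has 47. Then 47 × 1.25 = 58.75, so 59 per arm. The plan's figures reproduce.

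**4. Illustration of a one-arm shift.** The documents give no size for a same-day effect. I assume a shift b of 1 or 2 points on the planning scale.

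SE = 6.76 × √(2 × 1.25 / 59) = 1.39

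With no true effect, rejection rate = Φ(b/SE − 1.96) + Φ(−b/SE − 1.96). If instead the planned 3.90 contained the shift, power for the remainder = Φ((3.90 − b)/SE − 1.96).

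| Assumed shift b | Rejection rate, no true effect | Power for true effect 3.90 − b |
|---|---|---|
| 0 | 5.0% | 80% |
| 1 | 11.1% | 55% |
| 2 | 30.1% | 28% |

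**5. Sensitivity.** Three homes per arm and 59 residents retained give 59/3 = 19.7 per home. At the plan's intracluster correlation of 0.05, the design effect is 1 + 18.7 × 0.05 = 1.93. The rejection rates become 8.9% and 21.2%. The direction is the same and the size smaller.

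**The case against.** The strongest reply is that the order is inferred. Section 3.7.2, 3) is laid out by arm: intervention, then control, then the assessment common to both. That layout would look the same whichever came first. Section 3.7.2 is also not strictly chronological elsewhere: the education part describes twelve weeks of follow-up before the pamphlet, which Table 3.4 places at the first meeting. This stands. The documents do not prescribe coaching first. They list it first in two places and leave the order open.

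A reader might infer that T3 is affected in the same way. The documents do not support that. The group session belongs to the week-4 meeting. Both arms are reminded at week 12, and Evaluation is the first word in both cells, so measurement first is a fair reading there. The week-4 session is part of the programme, so any effect of it that lasts to week 12 is programme effect and not bias.

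A reader might also infer that T2 records coaching in place of the four-week effect. That goes too far. DFSBS items 1 to 7 cover the past 7 days and the quality-of-life scale the past four weeks. A same-day session can change how that period is reported but cannot create the behaviour.

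Finally, SD 6.76 is not a DFSBS value. It comes from the earlier health-promotion study cited in section 3.5.2, whose foot self-care tool, according to section 2.3.6, was developed by its own researchers. The DFSBS metric is itself unsettled: 1 to 5 per item in section 3.6.1, 0 to 7 in the printed questionnaire. The rejection rates therefore cannot be read as DFSBS results.

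**Conclusion.** The point holds for T2. At week 4 one arm is coached at the measurement visit, the coaching is listed first in both the table and the text, and nothing requires the questionnaire to come first. If the listed order is followed, T2 combines the four-week effect with a same-day booster in the intervention arm, and the planned analysis cannot separate them. KFC, FCCS and FCOE are most exposed. DFSBS is open to reporting bias, most in items 8 to 16. At T3 the same gap in wording exists, but the asymmetry is only in what the reminder is about.

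The size is unknown. The figures of about 11% and 30% rest on an assumed shift of 1 or 2 points, the plan's SD from another instrument, and its design effect of 1.25. They show only that a shift well below the planned 3.90 could matter. The conclusion also depends on staff following the listed order.

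**What to change.** In section 3.7.2, 3) and 4), and in the week-4 and week-12 rows of Table 3.4, state that in both arms every resident completes all questionnaires individually at the start of the visit. This comes before any sharing session, questions, guidance or reminder, with pamphlets and hand-outs put away. The session or reminder begins once the last questionnaire at that home is collected.

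The cost is a change of wording and a reordering of the same visit. The programme content, sample size and number of visits stay as they are. When editing these rows, reconcile two related points. Table 3.4 allows 20 minutes for discussion and questionnaire together, while section 3.6.2.2 expects about 30 minutes for the questionnaire alone. Section 3.7.2, 4) places the post-test after 8 weeks, while Table 3.4 places it at week 12.

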### **3.8 Ethical considerations**

Ethical approval of conducted research is very important as it deals with human and one's privacy. The necessary ethical approval will be obtained before the research project from The Ethics Committee for Research Involving Human Subjects Universiti Putra Malaysia (JKEUPM) (Reference number: XXX) and Department of Social Welfare/ Jabatan Kebajikan Masyarakat Malaysia (JKMM) as well as Ministry of Women, Family and Community Development (MWFCD) ethical committee (Reference number: JKMM XXX) will be attempted. If required, Good Clinical Practice (GCP) certificate will be attached in the ethic application form.

A formal letter from the Head of Community Department, Faculty of Medical and Health Sciences, UPM to the director of the JKMM seeking permission will be given prior of data collection (Reference number: attachment XXX). Subsequently, copy of all letter will be courtesy copy (cc) to the director of each RSK in peninsular Malaysia so as all the staff will be aware about the study.

The respondents will be explained about the topic of study. In order to assist the respondents in understanding the reason for the study, both information sheet and consent form will be written in two languages; Malay and English. An information sheet describing the study in the language of respondents' choice will be given to them to read or will be read to them by the researcher prior to written consent taking. All respondents who want to involve in this study must be voluntary and they are free to turn down to be included in this study without comment or penalty.

Full confidentiality and anonymity of the data will be maintained. All the information will be kept in a private envelope and soft data will be entered into a secured computerized database.

### **3.9 Data analysis/management**

The data collected will be analysed using the descriptive and inferential statistics. Statistical Packages for the Social Sciences version 22 for Windows will be used. Data screening will be performed to check the accuracy of data entry and to make sure that there is no missing value. Statistical test used are descriptive and inferential test. The level of significance will be set at  $p < 0.05$  (two-tailed) for all inferential analysis. The statistical report and conclusion will be written using APA style format.

Firstly, factor analysis will be used as a data reduction techniques to reduce a large number of variables to smaller set underlying factors that can summarizes the essential information contained in the variable and this procedure called as factor analysis (Coakes & Steed, 2003). The responses to the items of FCCS, and FCOE will be subjected to principal component analysis to identify underlying dimensions or factors. A threshold of 0.60 will be used to determine which statements are considered to be part of a factor. Internal consistency or reliability acceptable results for each factor and items that will be tested by Cronbach's alpha is acceptable as the alpha values for all the factors are above 0.80.

The demographic data and clinical characteristics will be analysed with descriptive statistics. The mean and standard deviation (SD) for continuous variables and the count (n) and percentages (%) for the dichotomous or nominal data (categorical data) will be calculated.

Meanwhile, to answer the hypothesis testing, an inferential statistics such as chi-square, mixed design analysis of variance (ANOVA) and repeated measure analysis of variance (RM-ANOVA) (if all statistical assumption for parametric tests are meets) will be used to compare the effectiveness before and after the intervention program. Table 3.5 showed the type of analysis that will used for each research objectives.

Table 3.5 Type of analysis based on research objectives.

| Objective                                                                                                                                                                                                                                                                                                                                                                                                                                                                                  | Type of analysis                                                                                                                                                                                                                                                                     |
|--------------------------------------------------------------------------------------------------------------------------------------------------------------------------------------------------------------------------------------------------------------------------------------------------------------------------------------------------------------------------------------------------------------------------------------------------------------------------------------------|--------------------------------------------------------------------------------------------------------------------------------------------------------------------------------------------------------------------------------------------------------------------------------------|
| 
Objective 1
 
To determine the:
 
 
demographic data of respondents
 
clinical characteristics of respondents
 
foot self-care behaviour of respondents
 
foot care efficacy expectation of respondents
 
foot care outcome expectation of respondents
 
knowledge on diabetes foot care of respondents
 
quality of life of respondents
 
                                               | 
Descriptive (mean, SD) and (n, %)
 
Descriptive (mean, SD) and (n, %)
 
Descriptive (mean, SD)
 
Factor analysis, Descriptive (mean, SD)
 
Factor analysis, Descriptive (mean, SD)
 
Descriptive (mean, SD) and (n, %)
 
Descriptive (mean, SD)
 |
| 
Objective 2
 
To determine the effects of self-efficacy enhancing program on quality of life, knowledge on diabetes foot care, foot care efficacy expectation, foot care outcome expectation and foot self-care behaviour of elderly with diabetes between group (intervention and control) at Time 1 (before the intervention education program), Time 2 (four weeks after the intervention education program) and Time 3 (12 weeks after the intervention education program)
 | 
Mixed between-within subjects ANOVA to examine the differences between two independent groups (intervention and control) while subjecting participants to repeated measures between T1, T2 and T3.
                                                                            |
| 
Objective 3
 
To determine the effects of self-efficacy enhancing program on quality of life, knowledge on diabetes foot care, foot care efficacy expectation, foot care outcome expectation and foot self-care behaviour of elderly with diabetes within group (intervention and control) at Time 1 (before the intervention education program), Time 2 (four weeks after the intervention education program) and Time 3 (12 weeks after the intervention education program)
  | 
RM-ANOVA to examine the differences in the outcomes between T1, T2 and T3. F tests with paired t tests to identify when changes in outcomes will take place.
                                                                                                                  |

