### 3.5 Sample

#### 3.5.1 Sampling method

A probability cluster sampling with specific eligibility criteria will be used in this study. There are nine RSK in the Peninsular Malaysia. However, for the time being, RSK Negeri Sembilan was closed due to renovation process, so there are total eight of RSK in Peninsular Malaysia. RSK Cheras will be excluded for pilot testing and RSK Pengkalan Chepa located in West Peninsular Malaysia. Hence, six RSK will be allocated randomly using random sequence number generator where each group (RSK) is having equal chance to be neither in the intervention group nor control group. Here, there are three RSK will be taken in intervention group and another three RSK will be placed under control group. Figure 3.2 showed how the sample will be selected and grouped in this study.

[figure not shown]

Figure 3.2 Sampling selection process

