### 3.5.2 Sample size calculation

The sample size estimation, which is carried out using hypothesis testing two population means (Aday & Cornelius, 2006). The data is taken from a previous study conducted by Chen et al. (2011). The baseline score was; mean=32.32 with standard deviation (SD) 6.76, post intervention score has increased to 36.22 with SD 6.95. The hypothesis of no difference is to be tested at the 5% ( $\alpha$ ) 0.05 level of significance and power ( $1-\beta$ ) = 0.80 (80%) (2-tailed). The hypothesis testing two population means sample size estimation as follow:

$$H_0 : \mu_1 = \mu_2$$

$$H_1 : \mu_1 \neq \mu_2$$

$$n = \frac{2\sigma^2 [Z_{1-\alpha/2} + Z_{1-\beta}]^2}{(\mu_1 - \mu_2)^2}$$

$\mu_1$  = estimated mean (larger)

$\mu_2$  = estimated mean (smaller)

$$n = \frac{2(6.76)^2 [1.96 + 0.842]^2}{(36.22 - 32.32)^2}$$

$$n = \frac{(91.40) (7.85)}{15.21}$$

$$n = 47$$

The above sample size formula is valid only for the simple random or systematic random sampling method. This study will employ a cluster sampling design, so it requires a larger sample size to achieve the same precision and power (Aday & Cornelius, (2006).

Therefore, the calculated sample size using the above formula need to be multiplied by the design effect (DEFF). According Aday & Cornelius, (2006), the DEFF =  $1 + (b - 1) roh$ , where  $b$  = cluster size and  $roh$  = rate of homogeneity (intracluster correlation). Assuming a cluster size of 6 and intracluster correlation of 0.05 (Davies et al., 2008), so the DEFF is 1.25. This means that such cluster sampling requires double the sample size of above,  $n = 47 \times 1.25 = 59$  of respondents is needed for each group.

Hence, a total of 71 are considered adequate to recruit for a dropout rate and potential of attrition (20%). Thus, total 142 eligible criteria of the respondents is needed to be approached in order to retain 118 respondents (59 respondents per group) at the end of the study.

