| Preliminary data/ assessment        | Screening
Blood sugar level testing (FBS)
Independence level (Katz Index)
Cognitive level (ECAQ)
Depression level (GDS)                                                                                                                                                                                                                                                                                                                                                                                          | Taking blood
Questionnaire                                                                                                                                               | 20 minutes                  |            |
|                                     | Consent form
The respondents need to fill in the questionnaire; demographic data, clinical characteristics, DFSBS, FCCS, FCOE, KFC, FS-QOL
Respondent will be randomly allocated                                                                                                                                                                                                                                                                                                                                              | Consent form
Questionnaire                                                                                                                                               | 20 minutes                  |            |
| Time                                | Activities                                                                                                                                                                                                                                                                                                                                                                                                                                                                                                                          |                                                                                                                                                                             | Mode of program             | Duration   |

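### Whole homes are randomised but no planned test accounts for home; at the protocol's ICC of 0.05, an arm comparison at one visit then has about 16–18% type I error, not 5%

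*Combined protocol and SAP*

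**What the plan says.** Section 3.5.1 makes the home the unit of randomisation: "six RSK will be allocated randomly using random sequence number generator", and "there are three RSK will be taken in intervention group and another three RSK will be placed under control group". Section 3.5.2 recognises that the simple two-means formula does not suit this design. It multiplies the result by a design effect of 1.25, taken from an ICC of 0.05 and a cluster size of 6.

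Section 3.9 sets out the inference. It lists "an inferential statistics such as chi-square, mixed design analysis of variance (ANOVA) and repeated measure analysis of variance (RM-ANOVA". Table 3.5 gives the between-group objective a "Mixed between-within subjects ANOVA to examine the differences between two independent groups (intervention and control" across T1, T2 and T3, and the within-group objective an RM-ANOVA with paired t tests. No term for home, cluster-level summary, GEE or cluster-robust variance appears anywhere. The only condition is a general proviso that parametric assumptions be met, with no alternative named.

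The baseline row of Table 3.4 says "Respondent will be randomly allocated", which reads as individual allocation and conflicts with section 3.5.1.

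**The concern.** Residents of one home share staff and services (section 1.3.3). In the intervention arm they also share the group seminar, staff reminders and the week-4 group session (section 3.7.2). The plan accepts this dependence when it sizes the trial and drops it when it tests. With three homes per arm, the between-arm error has 4 degrees of freedom at home level (6 − 2). An individual-level ANOVA on 118 residents uses 116.

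At stake is the between-group objective for the primary outcome, foot self-care behaviour, and for the four secondary outcomes. Standard errors would be too small, and a chance difference among six homes could be reported as an effect of the program.

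**Working it through.** **Inputs from the documents.** Six homes, three per arm (3.5.1). Two-sided alpha 0.05, power 80%, difference 36.22 − 32.32 = 3.90, SD 6.76, ICC 0.05, stated cluster size 6, 118 residents retained of 142 approached (3.5.2).

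**The plan's own figure.** n = 2 × 6.76² × (1.96 + 0.842)² / 3.90² = 47.2, taken as 47. DEFF = 1 + (6 − 1) × 0.05 = 1.25, and 47 × 1.25 = 58.75, taken as 59. Adding 20% gives 59 × 1.2 = 70.8, taken as 71 per arm, or 142 in total. This reproduces.

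**Residents per home.** 118/6 = 19.7 and 142/6 = 23.7. The stated cluster size of 6 matches the number of homes, not the residents in each.

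**Type I error of an arm comparison at one visit that ignores home.** Size = 2 × [1 − Φ(1.96/√DEFF)], with DEFF = 1 + (b − 1) × ICC.

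- b = 19.7, ICC 0.05: DEFF = 1.933, √DEFF = 1.39, 1.96/1.39 = 1.41, size 15.9%.
- b = 23.7, ICC 0.05: DEFF = 2.133, size 18.0%.
- b = 6 as stated, ICC 0.05: DEFF = 1.25, size 8.0%.

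The ICC is a planning assumption. At b = 19.7, the size at other assumed values is:

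| ICC | 0.01 | 0.02 | 0.03 | 0.05 | 0.10 |
|---|---|---|---|---|---|
| Size | 7.2% | 9.4% | 11.7% | 15.9% | 24.7% |

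**The planned tests over three visits.** Their size also depends on how far a home's effect persists from visit to visit, which the documents do not give. Null trials were simulated with 118 residents in six homes, ICC 0.05 and an assumed within-person correlation of 0.6 (4,000 per scenario):

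| Correlation of home effects over time | 1.0 | 0.8 | 0.5 | 0 |
|---|---|---|---|---|
| Arm comparison at week 12 | 15% | 16% | 17% | 15% |
| Mixed ANOVA, group main effect | 19% | 18% | 16% | 11% |
| Mixed ANOVA, group-by-time | 5% | 12% | 26% | 38% |
| Within-arm RM-ANOVA | 5% | 12% | 24% | 38% |
| Within-arm paired t test, T1 v T3 | 5% | 10% | 17% | 27% |
| t test on six home means, week 12 | 5% | 4% | 5% | 5% |

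A second simulation, with 20 residents per home and within-person correlation 0.5, gave 22%, 19% and 17% for the group main effect at correlations 1.0, 0.8 and 0.5, and 5%, 12% and 22% for group-by-time. At ICC 0.01 (118 residents, within-person correlation 0.6), group-by-time was 5%, 7% and 9% at the same correlations.

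**Power of an analysis on six home means.** Variance of a home mean = 6.76² × (0.05 + 0.95/19.7) = 4.49. SE of the difference = √(2 × 4.49/3) = 1.73. Noncentrality = 3.90/1.73 = 2.25. Against the 4-df critical value of 2.776, power is about 41% (about 59% at ICC 0.01). No baseline adjustment is assumed.

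**The case against.** A reader might infer that every planned test runs at 16% or more. The documents do not support that. A home effect that is constant over time cancels from group-by-time, from the within-arm RM-ANOVA and from the paired t tests, and these then hold 5%. Without home-by-visit variance their size cannot be fixed: it may lie below or above 16%.

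The 16–18% also belongs to a comparison that the analysis column of Table 3.5 does not name. The objective's wording refers to groups at each of three times, so a per-visit test is implied at most. In a pre/post design the program effect is usually read from group-by-time, while the main effect averages in the baseline visit. This stands, and it limits what the headline figure describes.

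The ICC of 0.05 comes from a cited study. The plan does not say which outcome it was estimated on and gives none for the secondary outcomes. The protocol's own cluster size of 6 yields only 8%. The ICC caveat stands, hence the range. The cluster size does not rescue the plan: 118 residents in six homes cannot average six each, and 8% is still above 5%.

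The proviso about parametric assumptions is no remedy, because allocating homes breaks independence by design and no other test is named. The Table 3.4 wording changes the size of no test; it is a contradiction to be reconciled.

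**Conclusion.** The omission is certain: homes are randomised, clustering enters the sample size, and no planned test accounts for home. Its size is conditional. For an arm comparison at one visit, type I error is about 16–18% at ICC 0.05 with 20–24 residents per home, and standard errors at that visit are too small by a factor of about 1.39 (b = 19.7). The group main effect is inflated similarly, to about 16–22% in the simulations, when home effects correlate 0.5 or more over time. Group-by-time is valid only under fully stable home effects; it reaches about 12% at correlation 0.8 and 22–26% at 0.5. The within-arm tests behave in the same way. These three-visit figures rest on assumed within-person correlations of 0.5 or 0.6. Since the plan gives no basis for assuming stable home effects, the analysis needs changing before results are seen.

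**What to change.** In Table 3.5, replace the mixed ANOVA for the between-group objective with one of two prespecified analyses:

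- a linear mixed model with random effects for home, home-by-visit and resident, and Satterthwaite or Kenward-Roger degrees of freedom (about 4 for the arm contrast); or
- a t test on the six home-level means of the baseline-adjusted score, with 4 df and critical value 2.776.

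These are alternatives and are not identical when home sizes differ. In Table 3.1 the six eligible homes run from 72 + 74 = 146 residents (Kangar) to 193 + 99 = 292 (Bedong). A permutation test over homes should not be the main test: three versus three gives 20 allocations, so the smallest two-sided p is 2/20 = 0.10.

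Report the estimated ICC for each outcome. Reconcile the allocation wording in Table 3.4 with section 3.5.1.

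The cost is text and a different procedure; no new data are needed. The statistical price is real and should be stated. At one visit, with ICC 0.05 and no baseline adjustment, intervals become about twice as wide (2.776 × 1.39 = 3.86, against 1.96). Power for 3.9 points is about 41% rather than 80%. Baseline adjustment may recover some of this, but the documents give no correlation from which to say how much. Restate the power statement in section 3.5.2 accordingly.
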